## Abstract

**Introduction::**

Cognitive deficits are considered a fundamental component of bipolar disorder due to the fact that they negatively impact personal/social functioning. Cognitive remediation interventions are effective in the treatment of various psychosocial disorders, including bipolar disorder. The use of Virtual reality as a rehabilitation tool has produced scientific evidence in recent years, especially in cardiovascular, neurological, and musculoskeletal rehabilitation. This study aims at evaluating the feasibility of a Cognitive Remediation Virtual Reality Program (CEREBRUM) for people with bipolar disorder in psychiatric rehabilitation.

**Material and Methods::**

Feasibility randomized controlled cross-over clinical study; we randomized 50 people from the Consultation and Psychosomatic Psychiatry Center of the University Hospital of Cagliari (San Giovanni di Dio Civil Hospital) with a diagnosis of bipolar disorder. We propose a cognitive remediation program in virtual reality (CEREBRUM), 3 months with 2 weekly sessions, for the experimental group and a usual care program for the control group (psychiatric visit and/or psychotherapy).

**Results::**

The results of the trial will be published in international peer-reviewed journals and will be disseminated at international meetings and congress.

**Discussion::**

This RCT aims, with regards to its feasibility and design, to provide information about a confirmatory trial that evaluates the effectiveness of a Virtual Reality Cognitive Remediation program in psychiatric rehabilitation for the treatment of cognitive dysfunction in people with bipolar disorder.

**Conclusion::**

The results that we analyzed at the end of the RCT will have an impact on psychiatric rehabilitation research with a focus on improving the application of technologies for mental health.

Trial registration: ClinicalTrialsgov NCT05070065, registered on September 2021.

## INTRODUCTION

1

Bipolar disorder is a range of chronic diseases characterized by recurrent episodes of mania/hypomania, depression, and euthymia (mood dysregulation); dysregulation in sleep/wake rhythm, and medical and psychiatric comorbidities [1]. Community surveys found that the lifetime prevalence of Bipolar disorder ranges between 1% and 2.4%, although the methodology of published studies may underestimate its prevalence [2]. The disease is highly disabling due to its early onset, severity and chronicity: it is considered one of the leading causes of disabilities in the world [3], accounting for 7.0% of all DALY’s due to mental and substance use disorders [4-6]. Alongside effective symptoms, cognitive impairment is believed to be a core component of bipolar disorder [7], and in the long-term bipolar disorder was found to be associated with a high risk of dementia [8, 9]. Overall, approximately 40% to 60% of people that experienced one or more episodes of bipolar disorder have neurocognitive impairment [10]. Neurocognitive dysfunctions may be found in premorbid stages, before the disease onset [11], in the early course of the illness [12], and during the euthymia phase [13]. Poor cognitive performance impacts negatively on occupational and social functioning [14], increases the hospital admissions, affects direct/indirect healthcare related costs [15], hinders the benefits of psychotherapy [16], and represents a barrier to achieving adequate social and occupational functioning and a good quality of life [17]. The affected domains included attention, processing speed verbal learning/memory, memory, and executive functions including cognitive flexibility, inhibitory control, and working memory [18, 19]. Despite the growing attention paid to identifying and treating cognitive impairment in bipolar disorder, evidence is still lacking on effective interventions aiming to minimize cognitive symptoms in these patients [20]. Lithium was deemed to have an indirect positive effect on cognition in bipolar disorder, but other drugs used in the treatment of bipolar disorder entail cognitive side-effects related with extrapyramidal, sedative, anticholinergic, and blunting mechanisms [21]. The term Cognitive Remediation (CR) implies interventions based on behavioral training that aims to improve cognitive processes (memory, attention, executive functions, social cognition, and metacognition), which have to be exerted long enough to guarantee the persistence of the results and their generalization [22]. Different approaches were used, ranging from paper-and-pencil to computerized-based rehabilitation program to mixed interventions [23, 24]. Initial evidence suggests that CR and physical activity may exert protective effects for the prevention of cognitive decline [25], and CR has been found to be effective in the treatment of various psychosocial disorders (including bipolar disorder) to improve the cognitive and social-occupational domains, although the evidence base is still inconclusive [20, 26, 27]. Recently, Virtual reality (VR) emerged as a promising rehabilitation tool, with a growing number of studies suggesting that VR may facilitate learning and/or enhance different skills, thanks to the ability to make learning experiences real and ecological compared with traditional intervention techniques [28-30]. Current research on the clinical use of VR software has led to positive results, especially in cardiovascular, neurological, and musculoskeletal rehabilitation [31. 32]. In mental health, the evidence is limited to rehabilitation of social cognition in people with schizophrenia, and the psychotherapy of anxiety disorders and phobias, it is increasing the focus on the use of VR for CR interventions especially for schizophrenia and mild cognitive impairment [33]. To date, there are no studies in which VR was used as a CR intervention to improve the cognitive processes related with the personal and social functioning of people diagnosed with bipolar disorder. Given the ability of VR to facilitate and generalize the learning of the trained skill and its capacity to favor engagement in the task [30] and that CR may exert protective effects for the prevention of cognitive decline, therefore, it is important to promote randomized controlled clinical trials that evaluate the effectiveness of VR-implemented CR interventions. CEREBRUM is one of the first VR-implemented CR tools in the field of psychiatric rehabilitation in Europe, conceived, and designed by “PRoMIND - Services for mental health SRLS” (Rome) in association with “IDEGO - Virtual Psychology” (Rome).

### Objectives

1.1

#### Primary Objectives

1.1.1

Feasibility assessment of a confirmatory trial to evaluate the effectiveness of a VR-implemented cognitive remediation tool (“CEREBRUM”) for the treatment of cognitive deficits in people with bipolar disorder.

#### Secondary Objectives

1.1.2

Preliminary evaluation of the intervention’s safety, participant satisfaction, and clinical effectiveness.

## MATERIALS AND METHODS

2

### Study Design

2.1

This is a randomized, controlled cross-over clinical feasibility study. This study follows the CONSORT flow diagram extension for feasibility study [34]. The protocol has been written according to the Standard Protocol Items (SPIRIT checklist) [35].

### Participant Identification

2.2

The participants with psycho-social disabilities were recruited at the Consultation and Psychosomatic Psychiatry Center of the University Hospital of Cagliari (San Giovanni di Dio Civil Hospital).

*Inclusion Criteria:* age from 18 to 75; diagnosis of bipolar disorder according to DSM-IV [36]; both sexes; users who sign the informed consent; users under protection for which the informed consent is signed by the support legal administration.

*Exclusion Criteria:* The non-satisfaction with the inclusion criteria; *the presence of maniac/depressive phases;* the diagnosis of epilepsy or serious eye diseases, due to the risk associated with the excessive stimulation of virtual reality.

### Randomization

2.3

Eligible participants were randomized into two groups, using a computer-generated randomization list. The biometrician responsible for the randomization process was blinded to the identities of participants. The experimental group (A) receives the CR intervention with virtual reality (CEREBRUM) lasting 3 months (two weekly meetings) and the control group (B) receives treatment as usual. When group A receives the “CEREBRUM” intervention, group B receives treatment, as usual, 1 month after the end of the intervention for group A (washout period) group B receives the “CEREBRUM intervention becoming experimental group and group A the routine intervention (Table **1**).

### Blinding

2.4

The nature of the intervention does not permit the blinding of the participants or the mental health workers on the project.

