### Data collection

2.8

The data collection was made with a personal data sheet; consecutively the patients were enrolled at the Consultation and Psychosomatic Psychiatry Center of the University Hospital of Cagliari (San Giovanni di Dio Civil Hospital). The presence of possible side effects and satisfaction with the intervention was assessed through a self-report questionnaire, for the others, secondary outcome indicators were used, and a standardized evaluation tool validated in Italian and used in psycho-social research (in the case of a learning effect, different versions for retests were used). Participants were assessed before the treatment, after the end of the intervention, and after 6 and 12 months after the end of the intervention.

*For the cognitive evaluation was used:* Matrix test [38]; Rey Figure Test [39]; Rey's Words Test, in the two versions [40, 41]; Digital Symbol Substitution Test, in the two versions [42, 43]; Trail Making Test, in the two versions [44]; Normal and Inverse Digit Span, in the two versions [45, 46]; Stroop Test [47]; Frontal Assessment Battery - FAB [48]; Phonological and Semantic Verbal Fluency Test, in the two versions [41, 49]; Test of Cognitive Estimates (CET), in the two versions [50, 51]; Test of the Tale [52, 40].

*For the general evaluation was used:* SF-12, Short Form Health Survey with 12 items [53], a self-administering scale, which investigates the following dimensions of well-being: vitality, physical function, physical pain, perception of general health, mental health, physical and emotional, work functioning, and social role. TAS-20 Toronto Alexithymia Scale [54] self-administering scale, evaluates the level of emotional awareness. Self-Rating Scale (SAS) self-administered scale [55] evaluates perceived anxiety levels regardless of diagnosis. The Patient Health Questionnaire - PHQ-9, self-administering scale [56], evaluates depressive symptoms. Health of The Nation Outcome Scale - HoNOS [57] evaluates personal and social functioning and clinical performance. Biological Rhythms Interview of Assessment in Neuropsychiatry - BRIAN validated in Italian version [58], an interview consisting of 18 items that investigates 4 main areas related with the dysregulation of circadian rhythms (sleep, activity, social rhythms, and nutrition).

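### The reason given for not blinding project workers does not extend to outcome assessment, so the secondary effectiveness estimates from HoNOS, the BRIAN interview and the examiner-scored cognitive tests may be biased towards CEREBRUM

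*Protocol article*

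**What the plan says.** Section 2.4 (Blinding) of the protocol article reads in full: "The nature of the intervention does not permit the blinding of the participants or the mental health workers on the project". It makes no exception for outcome assessors.

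The only masking described is in section 2.3 (Randomization): "The biometrician responsible for the randomization process was blinded to the identities of participants". This concerns the allocation list and has no bearing on how outcomes are rated.

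Section 2.8 (Data collection) labels SF-12, TAS-20, SAS and PHQ-9 as self-administered. Side effects and satisfaction are also self-reported: "The presence of possible side effects and satisfaction with the intervention was assessed through a self-report questionnaire". Three other kinds of measure do not carry that label:

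- "Health of The Nation Outcome Scale - HoNOS [57] evaluates personal and social functioning and clinical performance".
- BRIAN, described as "an interview consisting of 18 items that investigates 4 main areas related with the dysregulation of circadian rhythms".
- A battery of 11 cognitive tests, including "Frontal Assessment Battery - FAB [48]; Phonological and Semantic Verbal Fluency Test, in the two versions [41, 49".

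The section does not say who performs these assessments. Their timing is given as: "Participants were assessed before the treatment, after the end of the intervention, and after 6 and 12 months after the end of the intervention".

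Section 1.1.2 sets the rank of these measures: "Preliminary evaluation of the intervention’s safety, participant satisfaction, and clinical effectiveness".

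**The concern.** The sentence in 2.4 justifies the absence of blinding by the nature of the intervention. Someone wearing a headset, or running the session, necessarily knows that CEREBRUM is being given. Someone who conducts the BRIAN interview, completes HoNOS or scores a fluency sheet need not know. As worded, the section gives up masking for project workers as a group, for a reason that fits only some of the tasks they may perform.

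A rater who knows the group and period can lean towards the recently treated participant in prompting, timing or judgement. The crossover does not remove this. If the lean favours whoever has just had CEREBRUM, it enters both periods in the same direction and is indistinguishable from a treatment effect. The performance-test scores are the dependent variables that section 2.10 (Data Analysis) names for the MANOVA, so the exposed measures include those that carry the effectiveness analysis. The trial is also meant to inform the design of a confirmatory trial, which could inherit the premise that masked assessment is impossible.

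**Working it through.** **Step 1. Which measures depend on a rater (section 2.8).**

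| Measure | Described as | Open to rater bias? |
|---|---|---|
| SF-12, TAS-20, SAS, PHQ-9 | self-administered | no; exposed through unblinded participants instead |
| side effects, satisfaction | self-report questionnaire | no; same remark |
| BRIAN | interview | yes, through judgement |
| HoNOS | no self-administered label | yes, through judgement, if rated by staff |
| 11 cognitive tests | standardized tests | to a varying degree: timing, prompting, scoring |

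The coprimary outcomes in section 2.7 are the proportion recruited among those eligible and the proportion completing the intervention. Neither is rater-scored.

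**Step 2. Does the reason in 2.4 reach each role?** Participants: yes. Workers delivering sessions: yes. People who administer or score outcomes: no, unless they also deliver the sessions. No section provides masked or independent assessment.

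**Step 3. Why the crossover does not cancel the bias.** Let raters add b to whichever group has just had CEREBRUM, with no true effect. The A minus B difference is +b in period 1 and −b in period 2, because B is then the treated group. The crossover estimate is half the difference of the two: (b − (−b))/2 = b. The bias passes through whole.

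**Step 4. Illustration of size.** The article gives no alpha, power, SD, correlation or effect size, so there is no stated figure to reproduce. Input from the article: 50 randomized (section 2.11). Assumptions: 25 per group, all 50 analysed, no true effect, two-sided 5% test, b = 0.1, 0.2 or 0.3 SD, and within-person correlation rho of 0.5 or 0.7.

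Formula: P(reject) = P(Z > 1.96 − b/SE) + P(Z < −1.96 − b/SE).

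- 25 v 25 after period 1: SE = sqrt(2/25) = 0.283 SD.
- Within-person, rho 0.5: SE = sqrt(2 × 0.5/50) = 0.141 SD.
- Within-person, rho 0.7: SE = sqrt(2 × 0.3/50) = 0.110 SD.

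| Comparison | b = 0.1 SD | b = 0.2 SD | b = 0.3 SD |
|---|---|---|---|
| 25 v 25 | 6.4% | 10.9% | 18.6% |
| 50 within-person, rho 0.5 | 10.9% | 29.3% | 56.4% |
| 50 within-person, rho 0.7 | 15.0% | 44.7% | 78.2% |

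Example: 25 v 25 with b = 0.3 gives b/SE = 1.061, so P(Z > 0.899) + P(Z < −3.021) = 18.4% + 0.1%, which is 18.6% before rounding of the two terms. Nearly all the excess lies in the direction that favours CEREBRUM. The more precise the comparison, the more often a fixed bias reaches significance.

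**The case against.** The strongest reply is that 2.4 refers to mental health workers, a term that may mean only those who deliver care; section 2.5 calls the person monitoring a session a health worker. On that reading the sentence is true and simply silent on assessors, and a condensed article may leave assessors to the full protocol. Part of this stands: the article never says who rates, so a risk is left open and no bias is shown. A reader might infer that treating staff rate their own participants, or that every project member is unblinded. The documents support neither: section 2.8 names no assessor, and the randomization biometrician is blinded to identities. But the sentence covers the mental health workers on the project without exception and gives a reason. If masked assessors exist in a fuller document, the published sentence still needs narrowing.

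Second, only secondary, preliminary outcomes are affected, and the sample is justified by recruitment and retention. This stands and limits the weight of the point.

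Third, the sizes are assumed. This also stands. One bias value is applied to all measures, although timed or standardized tests are less susceptible than HoNOS or BRIAN. The larger percentages belong to a within-person contrast that section 2.10 does not state; it describes a MANOVA by time and group.

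Fourth, separating rating from delivery is not the same as masking. Participants may disclose their group, and the CEREBRUM blocks run one after the other, so a rater who knows the calendar can often infer the group. Staffing is not described, and section 2.12 reports that participants are already receiving the programme, so a new rater could differ from the one at baseline. These points stand against the rostering step. They do not touch label-free scoring, coded analysis groups or honest labelling.

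**Conclusion.** The point holds as a matter of wording and of an available safeguard not provided. The reason in 2.4 does not justify unmasked outcome assessment, and nothing in the article masks whoever rates or scores HoNOS, BRIAN and the cognitive tests. The corresponding effectiveness estimates may therefore be biased towards CEREBRUM. The feasibility conclusions on recruitment and completion are untouched.

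No bias size can be derived from the documents. Under the stated assumptions, a bias of 0.1 to 0.3 SD would raise the two-sided 5% error to about 6% to 19% (25 v 25), 11% to 56% (50 within-person, rho 0.5) or 15% to 78% (rho 0.7). These figures show sensitivity and do not estimate what will happen. Masked assessment would not cure the exposure of the self-report scales, which comes from unblinded participants.

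**What to change.** 1. Limit the statement in 2.4 to participants and the workers delivering CEREBRUM, and say who administers and scores the outcomes.
2. Score the recorded test sheets (such as fluency, Rey, tale, CET and FAB) from coded records without group, period or visit labels.
3. Give the analyst coded groups.
4. Where existing staffing allows, have the remaining HoNOS, BRIAN and cognitive assessments done by a current worker who does not deliver CEREBRUM to that participant, keeping the same rater across a participant's visits where possible.
5. Where step 4 cannot be done, report HoNOS and BRIAN as unblinded alongside the results.

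Steps 1, 2, 3 and 5 need revised protocol wording, coded sheets and a reporting label, with no new post. Step 4 costs scheduling effort and may change the rater between visits in a trial already under way; its feasibility depends on staffing that the article does not describe. Masking will remain incomplete because participants may disclose their group and the treatment blocks are sequential.

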### Intervention

2.5

CEREBRUM is Immersive Virtual Reality software, developed by professionals and experts operating in the field of cognitive rehabilitation (psychiatric rehabilitation technicians and psychologists). It is compatible with the Oculus Go virtual reality viewer, a device with CE obligation. The CEREBRUM App allows the user to immerse themselves in experiential situations that simulate everyday reality, useful for working on users' resources, and difficulties. The user wearing the viewer sees a virtual environment that can be explored at 360 °. The user does not interact with the virtual environment but explores the scene and answers the rehabilitator's questions. It reinforces the improvements obtained from an intervention based on the Cognitive Remediation approach, also allowing direct monitoring by the health worker.

The CEREBRUM App consists of 52 exercises of varying difficulty: 22 belonging to the Memory, and Learning Module, 10 to the Cognitive Estimates Module and 20 to the Attention and Working Memory Module.

The different degrees of difficulty are designed to adapt to the user's functional diagnosis. The clinician must adapt the difficulty level to the residual abilities of the user so that the exercises are neither too easy nor too complex.

The intervention involves 24 sessions of 45minutes, 2 sessions per week for 3months. Each session was structured as follows: Reception, psychoeducation and orientation to the tool; Exercise psychoeducation; Psychoeducation to the function trained by exercise; Generalization phase, in which the function and its importance in the context of life are explained to the person (a bio-psycho-socio-cultural approach based on cognition); Carrying out the exercise in VR with positive and corrective feedback; Post-exercise comment/return; Second exercise with the same method mentioned above; The exposure within the Virtual Reality must be a maximum of 15-20 minutes; Final return; Homework to leave, intended as practical suggestions that the patient must try to carry out during his day.

In general: 1 Attention and Working Memory exercise plus 1 Memory/Learning exercise or 1 Cognitive Estimation exercise. In some sessions, depending on the user, the session, and the operator's assessment, you can also do a third exercise belonging to any area.

### Control

2.6

The control group receives treatment, as usual, consisting of a psychiatric consultation with or without psychotherapy.

### Outcomes

2.7

The Primary outcome is defined as the proportion of patients recruited among those considered eligible. Coprimary outcome is the proportion of patients completing the trial intervention among those included.

Secondary outcomes:

Intervention’s safety: number of adverse events and severe adverse eventsPatients satisfactionClinical Effectiveness in improving the cognitive process, personal, and social functioning, levels of perceived anxiety, quality of life, emotional awareness, and psychopathological symptoms. An intervention protocol person-centered and recovery-oriented [37], is defined as a process of change through which the individual improves their health and well-being (lives in a “self-directed” way and is committed to living to the best of their potential), whether it may lead to a global improvement.

### Data collection

2.8

The data collection was made with a personal data sheet; consecutively the patients were enrolled at the Consultation and Psychosomatic Psychiatry Center of the University Hospital of Cagliari (San Giovanni di Dio Civil Hospital). The presence of possible side effects and satisfaction with the intervention was assessed through a self-report questionnaire, for the others, secondary outcome indicators were used, and a standardized evaluation tool validated in Italian and used in psycho-social research (in the case of a learning effect, different versions for retests were used). Participants were assessed before the treatment, after the end of the intervention, and after 6 and 12 months after the end of the intervention.

*For the cognitive evaluation was used:* Matrix test [38]; Rey Figure Test [39]; Rey's Words Test, in the two versions [40, 41]; Digital Symbol Substitution Test, in the two versions [42, 43]; Trail Making Test, in the two versions [44]; Normal and Inverse Digit Span, in the two versions [45, 46]; Stroop Test [47]; Frontal Assessment Battery - FAB [48]; Phonological and Semantic Verbal Fluency Test, in the two versions [41, 49]; Test of Cognitive Estimates (CET), in the two versions [50, 51]; Test of the Tale [52, 40].

*For the general evaluation was used:* SF-12, Short Form Health Survey with 12 items [53], a self-administering scale, which investigates the following dimensions of well-being: vitality, physical function, physical pain, perception of general health, mental health, physical and emotional, work functioning, and social role. TAS-20 Toronto Alexithymia Scale [54] self-administering scale, evaluates the level of emotional awareness. Self-Rating Scale (SAS) self-administered scale [55] evaluates perceived anxiety levels regardless of diagnosis. The Patient Health Questionnaire - PHQ-9, self-administering scale [56], evaluates depressive symptoms. Health of The Nation Outcome Scale - HoNOS [57] evaluates personal and social functioning and clinical performance. Biological Rhythms Interview of Assessment in Neuropsychiatry - BRIAN validated in Italian version [58], an interview consisting of 18 items that investigates 4 main areas related with the dysregulation of circadian rhythms (sleep, activity, social rhythms, and nutrition).

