### Sample Size Considerations

2.11

To date there is still poor evidence in this field of research for establishing an effective methodology in terms of sample size, and in this sense, the aim of this study is to verify the feasibility [20, 59]. We randomized 50 participants in order to be able to assess the feasibility outcomes: recruitment and retention rates Fig. (**1**).

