### Risk and Benefits

4.1

The use of immersive VR could have different side effects such as dizziness, nausea, headache, eye fatigue, reduced limb control, reduced postural control, reduced sense of presence, and development of inadequate responses to the real world. As a matter of fact, important side effects are not expected, as the VR tool has already been used in people with psychosocial disabilities, albeit for other purposes, without substantial side effects [60-64].

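### Safety is defined as a count of adverse and severe adverse events, but its only stated source is a self-report questionnaire on the presence of side effects, so the counts may be incomplete

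*Protocol article*

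**What the plan says.** All references are to the protocol article.

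- **Outcome.** Section 2.7 (Outcomes) lists safety first among the secondary outcomes and defines it as a count of adverse events and of severe adverse events. Section 1.1.2 names preliminary evaluation of safety as a secondary objective.
- **Source.** Section 2.8 (Data collection) gives one source: "The presence of possible side effects and satisfaction with the intervention was assessed through a self-report questionnaire". No other source of adverse event data is named.
- **Timing.** The same section lists the assessments: "Participants were assessed before the treatment, after the end of the intervention, and after 6 and 12 months after the end of the intervention". It does not say whether the questionnaire belongs to these visits.
- **Exposure.** Section 2.5 (Intervention): "The intervention involves 24 sessions of 45minutes, 2 sessions per week for 3months". It describes the tool as "also allowing direct monitoring by the health worker" and gives each session a comment step after the exercise. It does not link either to recording adverse events.
- **Expected effects.** Section 4.1 (Risk and Benefits) anticipates "dizziness, nausea, headache, eye fatigue, reduced limb control, reduced postural control", among others.
- **Non-completion.** Section 2.7: "Coprimary outcome is the proportion of patients completing the trial intervention among those included". No expected dropout rate is given.

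**The concern.** The outcome and the instrument are both stated, and they do not match. A form that records whether side effects were present does not, on that description, deliver the number of events. Side effects that a participant attributes to the intervention are also a narrower class than adverse events, and a poor route to severe ones.

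Three kinds of event are at risk of being missed:

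1. Short-lived symptoms such as dizziness or nausea, if they have to be recalled long after the session. The participants are people in whom the article itself (section 1) describes memory and attention deficits as common.
2. Events in participants who stop early, if they are not asked.
3. Severe events such as an admission or a new mood episode. Current manic or depressive phases are an exclusion (section 2.2), so a new episode is an obvious candidate.

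There is also a comparison problem. The questionnaire concerns the intervention. Each group also spends a period in usual care (sections 2.3 and 2.6), for which no event source is stated. Background events then cannot be separated from those that accompany VR.

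At stake is a stated secondary objective of a trial meant to inform a confirmatory one. If events are lost, the loss runs towards better apparent tolerability.

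**Working it through.** The article gives no safety figure, so there is nothing to reproduce. The check has two parts.

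**1. Outcome and source side by side**

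| Element of the outcome (2.7) | What the stated source offers (2.8) |
|---|---|
| Number of events | Presence of side effects |
| Adverse events of any cause | Side effects of the intervention |
| Severe events counted separately | No severity element mentioned |
| Both groups, both periods of the cross-over | A form about the intervention; nothing stated for usual care |

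On timing, 2 sessions per week for 3 months gives the stated 24 sessions. All of them fall between the first two listed assessments. If the form follows that schedule, recall reaches back up to 3 months. If it is given after each session, it does not. The article does not say which.

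**2. Possible size of the loss among those who stop (illustration only)**

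The one input from the article is N = 50 (section 2.11: "We randomized 50 participants in order to be able to assess the feasibility outcomes: recruitment and retention rates"). Everything else is assumed:

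- all 50 receive at least one session;
- a fraction d stops early;
- a share q of those who stop do so because of side effects, and the others who stop are unaffected;
- a fraction r of completers has side effects;
- only completers answer the form.

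Formulas:

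- completers n = 50 × (1 − d)
- affected completers = n × r; affected dropouts = (50 − n) × q
- observed proportion = (n × r) / n = r
- true proportion = [n × r + (50 − n) × q] / 50
- share of affected participants missed = (50 − n) × q / [n × r + (50 − n) × q]

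Ranges used: d from 10% to 30%, q from 25% to 100%, r of 10% or 20%. Expected numbers need not be whole.

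| Case | d | q | r | Affected completers | Affected dropouts | Observed | True | Missed |
|---|---|---|---|---|---|---|---|---|
| Smallest loss | 10% | 25% | 20% | 45 × 0.20 = 9 | 5 × 0.25 = 1.25 | 20% | 10.25/50 = 20.5% | 1.25/10.25 = 12% |
| Middle | 20% | 50% | 10% | 40 × 0.10 = 4 | 10 × 0.50 = 5 | 4/40 = 10% | 9/50 = 18% | 5/9 = 56% |
| Largest loss | 30% | 100% | 10% | 35 × 0.10 = 3.5 | 15 × 1.00 = 15 | 10% | 18.5/50 = 37% | 15/18.5 = 81% |

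If those who stop are also asked, the middle case gives 9/50 = 18% and nothing is missed by this route. The result follows the assumptions, and the article supplies none of them. The table shows only that the answer to one unstated question, whether dropouts are asked, can matter a little or a great deal.

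**The case against.** The strongest reply is that this is a condensed article. Adverse event logging, severity grading and follow-up of withdrawals commonly sit in the full protocol, and their absence here does not show that they are absent from the trial. Staff run every session and could note events. The PHQ-9, the HoNOS and the psychiatric consultations of usual care give some view of clinical deterioration. The description of the questionnaire is one line about a form we have not seen, and it may ask about frequency or severity.

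Much of this stands, and it rules out three stronger readings that a reader might infer:

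- **That the form is given only at the scheduled assessments.** The sentence on assessment times follows the one on the questionnaire but does not refer to it. Use after each session is equally compatible with the text.
- **That people who withdraw do not complete it.** Nothing says they are left out.
- **That the form cannot yield counts.** The wording suggests a poor fit but does not prove it.

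The reply does not remove the mismatch. The article names an outcome and then names its source, and the source as described does not measure that outcome. The other channels are not adverse event recording: the PHQ-9 covers depressive symptoms, no scale specific to mania is listed, none of these is said to capture admissions, and section 2.5 ties no event record to the operator's presence. If the full protocol holds an adverse event procedure, section 2.8 should name it.

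**Conclusion.** The concern holds as a mismatch between the safety outcome and its only stated source, together with a risk of under-counting. It does not establish that safety is biased.

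The firm part is that a count of adverse and severe adverse events is said to come from a self-report form on the presence of side effects, with nothing stated for usual-care periods. The conditional part is the loss of brief symptoms and of events in those who stop, which depends on a timing and a coverage that the article does not give. The size cannot be derived from the document. The contrast of 10% with 18%, and the range of 12% to 81% of affected participants missed, apply only if dropouts are not asked and the assumed rates hold.

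This matters for a secondary, preliminary objective. It does not touch the two feasibility outcomes. It is worth correcting because the correction is cheap.

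**What to change.** Amend section 2.8 as follows.

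- At each session, the operator already present records adverse events on a short checklist: type, severity, and whether VR was stopped. The comment step after the exercise is a natural place for it.
- Severe events, including admissions and new mood episodes, are taken from the centre's clinical records in both groups and both periods.
- The reason is recorded for everyone who withdraws.
- Events during the intervention are counted in everyone with at least one session. Report event numbers, and per-participant proportions with exact confidence intervals.
- The questionnaire stays for satisfaction and as a supplement on side effects, with its timing and its use in those who stop stated.

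**Cost.** A few minutes per session, a records check at the same centre, and a small amendment to the forms; no extra staff. The reported event rate will probably rise, because more events are found. Section 2.12 says participants are already receiving the programme, so the checklist can cover only the remaining sessions, and the report should give the date from which it was used. The records check can reach back over earlier periods.
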